### Screening, recruitment and randomization

All RTR patients are screened for eligibility during the post-transplantation recovery period, so within 7–10 days after surgery, by the nephrologist. Eligible RTR are invited to participate, informed about the study protocol and if agreed are asked to participate and sign written informed consent. In case of non-Dutch or non-English speaking patients, interpreters are used.

In total, 219 participants (73 per group) will be recruited. The sample size is based on the expected improvement on the physical functioning scale of quality of life of 13.8 points in the intervention group and 8.8 points in usual care (α=0.05, β= 0.80, SD = 11.0) [26]. A difference of 5.0 points between the standard effect is considered a relevant effect. This results in a required number of 57 RTR per group. Taking into account a potential dropout rate of 15% and a correction for heterogeneity between centers of 10%, this results in a total required number of 73 RTR per group (*N* = 219 in total). Randomization to one of the three arms is computerized using the ‘PROC SURVEYSELECT’ function in the software program SAS (Cary, North Carolina, USA). It is performed by an independent data management company hosting the data entry facility, who are not involved in conducting the study itself (Nefrovisie foundation, Utrecht, the Netherlands). Participants are randomized by block randomization in groups of 6–9 for rehabilitation centers and in groups of 3 for physiotherapy practices.

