### Usual care

Participants randomized to the usual care group receive standard post-transplant care as usual in the hospitals. Current standard nutrition care after kidney transplantation consists of 1–4 inpatient consultations by a renal dietitian during the inpatient stay (7–10 days), followed by 1 outpatient consultation. During inpatient consultations attention is paid to optimal nutritional intake, maintaining a stable body weight and muscle mass, or increasing body weight when needed. After a few months, during the outpatient follow-up, attention is paid to maintaining a stable body weight, or increasing or decreasing body weight when needed. When a participant has increased cholesterol, (un)saturated fat intake is discussed, and mono/disaccharides are discussed when a participant has increased HbA1c. Likewise, salt consumption is discussed in case of increased 24-h sodium excretion. Exercise or lifestyle counseling are not included in the standard post-transplant care in either of the participating hospitals. Participants randomized to the usual care group receive general advice to meet the standard Dutch exercise guidelines (30 min of moderate physical activity per day) and follow the Dutch Dietary guidelines.

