### Exercise only intervention

The exercise intervention consists of two phases. The first phase is a 3-month exercise training program, followed by the second phase; a 12-month active follow-up with lifestyle counseling (Figure 2). Exercise training sessions are done in groups of 4–10 participants in the rehabilitation centers and with 1–6 participants in the physiotherapy centers.

The training program encompasses two exercise training sessions per week (21 exercise training sessions and 3 test sessions in total) and is focused on improving maximal muscle strength, local muscle endurance, and aerobic capacity. Each exercise training session consists of 30-min dynamic resistance training of all the major muscle groups (Additional file 1: Table S1) using resistance training machines, 30 min of aerobic training (cycle-ergometry and treadmill walking), and is concluded with a 30-min supervised sports activity or swimming, depending on the available facilities.

The dynamic resistance training includes both maximal strength training (relatively high load, fewer repetitions), and muscle endurance training (relatively low load, large number of repetitions).

Optimal resistance training load is determined using one-repetition maximum testing (1RM) for each participant. The content of the training program is in line with the American College of Sports Medicine guidelines exercise in healthy adults [27], and was previously shown to be effective in improving muscle strength and aerobic capacity in RTR [22]. The full resistance- and aerobic training program is shown in Additional files 1 and 2: Tables S1 and S2.

Maximal muscle strength (1RM) for all exercise machines (Additional file 1: Table S1) is assessed at baseline. For maximal muscle strength training, moderate loading is used (50–60% 1RM), for 2–3 sets of 8–10 repetitions. Higher loads are known to be more appropriate for maximal muscle strength, however 50–60% 1RM is used in our protocol as most participants are untrained, and RTR have increased risk of tendon ruptures. For local muscle endurance training a light-to-moderate load is used (25–35% 1RM), for 1–3 sets of 30 repetitions. All resistance exercise involved exercise machines, no free weights are used for safety reasons.

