### Exercise + diet intervention

The exercise training program in the exercise + diet intervention group is identical to that of the exercise intervention group, and additionally, participants receive dietary counseling. The dietary counseling runs throughout the entire 15 months of the study period and consists of a total of 12 counseling sessions with a renal dietician. The dietary counseling takes place in the hospital face-to-face. If this is not feasible some counseling sessions are done by phone. The dieticians are trained to use motivational interviewing techniques which they apply during the dietary counseling sessions.

Goals are set to improve nutrition status to preserve renal function, to prevent weight gain, type 2 diabetes, and hypercholesterolemia. These goals are set together with the participant to facilitate an autonomy supportive counseling climate [33]. A three-day food diary is used as input during the dietary consultations and for personal goal setting. Participants also receive a food logbook which contains information and exercises to help the participant set diet goals. During the dietary counseling sessions, special attention is given to salt intake, whole-wheat grains and fruit and vegetable intake, intake of saturated and unsaturated fat, and the use of sugar-rich products, sugar-sweetened beverages (soft drinks, sweetened dairy drinks and fruit juices) and preventing overeating. In addition, participants are reminded of their physical activity goals, and the importance of protein intake for maintaining and increasing muscle mass. In case of disease after transplantation, for example infections, the dietician assists the patient in maintaining an energy- and protein-rich diet to prevent further deterioration or decline in muscle mass.

Dietary counseling session 9 (of total 12) is a group meeting for which the participants are encouraged to bring significant others such as their partner or other supportive family members. The dietary counseling is in line with the 2006 Guidelines for a Healthy Diet by the Dutch Food and Nutrition Council [34], supplemented with diet guidelines for RTR [35] and diet guidelines for the prevention of type 2 diabetes [36] and cardiovascular risk [37].

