### Statistical analyses

Short term differences between groups will be tested using students T-test or linear regression, and long term differences will be tested using General Linear Mixed models. Time will be analyzed for exercise intervention (phase 1) and maintenance period (phase 2). Centers will be taken into account as random factor. Intention to treat principle will be applied in primary analyses. Per protocol analysis will be based on completion of the exercise training sessions, and attendance of dietary counseling sessions. Stratified analysis are foreseen for time after transplantation, socio-economic status and immunosuppressive regime. Furthermore, potential preset determinants of intervention outcome will be evaluated in a GLM model: gender, age, coping style, fear of movement, work participation and clinical factors.

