A limitation of the present study is its complexity. The RCT involves skills and experience of multiple healthcare professionals working at different centers, making it difficult to standardize intervention delivery. Another limitation is that the exercise intervention and exercise with dietary counseling groups are combined. This may lead to contamination between groups, as participants of the exercise + diet group may share dietary advice with the exercise only group e.g. during the exercise training sessions. Furthermore, participants entering the ACT trial already have a certain degree of motivation to improve their health and fitness through lifestyle. Therefore, control participants may have worked on their health and fitness in alternative ways. Another limitation is that the study took place only in the Netherlands.

The present study aims to provide evidence needed to guide decision making by clinicians and policy-makers in post-transplantation care. Furthermore, it will help develop guidelines for post-transplantation care in the Netherlands to further improve long-term outcomes of renal transplantation.

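### Training groups exist only in the exercise arms, but the only clustering term is a random centre factor, so standard errors against usual care may be somewhat too small

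*Protocol article*

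**What the plan says.** On delivery, the section on the exercise only intervention states: "Exercise training sessions are done in groups of 4–10 participants in the rehabilitation centers and with 1–6 participants in the physiotherapy centers". The next section adds: "The exercise training program in the exercise + diet intervention group is identical to that of the exercise intervention group". The Discussion lists as a limitation that the "exercise intervention and exercise with dietary counseling groups are combined", so patients of both arms attend the same sessions. For the control arm, the Usual care section states: "Exercise or lifestyle counseling are not included in the standard post-transplant care in either of the participating hospitals".

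On analysis, the Statistical analyses section names its methods by time frame: "Short term differences between groups will be tested using students T-test or linear regression, and long term differences will be tested using General Linear Mixed". It then gives the only clustering term: "Centers will be taken into account as random factor". It names no term for training group, exercise site or therapist.

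The sample size in the section on screening, recruitment and randomization includes "a correction for heterogeneity between centers of 10" per cent. The same section sets block sizes of 6–9 for rehabilitation centres and 3 for physiotherapy practices.

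**The concern.** Patients who train in the same group share a physiotherapist, a room and each other's company. According to the Professionals section, the supervising physiotherapist usually gives the lifestyle counselling too, and that counselling continues to month 15. Physiotherapists may make slight changes to training intensity, and the Discussion concedes that delivery is hard to standardise across professionals and centres. Some positive correlation of outcomes within groups or therapists is therefore plausible. Usual-care patients have no counterpart to it.

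Such one-sided clustering inflates the variance of the exercise-arm means but not of the usual-care mean. A centre intercept common to all arms drops out of a within-centre comparison and leaves this extra variance out of the standard error. A plain t-test or linear regression leaves it out as well. At stake are the width of the confidence intervals and the error rate of each exercise arm against usual care, including for the primary outcome, SF-36 physical functioning.

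**Working it through.** **The plan's own figures.** The inflation step reproduces: 57 × 1.15 × 1.10 = 72.1, rounded up to 73 per group. The 10% factor therefore adds patients; it does not enter the standard error of the analysis. (The 57 itself does not follow from a difference of 5.0, SD 11.0, α 0.05 and 80% power: the usual formula gives 76 two-sided or 60 one-sided. That is a separate point, and nothing below depends on it.) The plan gives no intraclass correlation (ICC) or design effect to reproduce.

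**Inputs**
- Group sizes 4–10 and 1–6, mixed across the two exercise arms (sections on the two interventions; Discussion).
- Blocks of 6–9 over three arms: 2–3 patients per arm. Blocks of 3: one per arm. If training groups follow blocks, a group holds m = 1 to 3 members of the same arm. A group of 10 split evenly between the two exercise arms gives m = 5.
- ICC: assumed 0.01, 0.05 and 0.10.
- Two-sided test at 5%: assumed, since sidedness is not stated.

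**Formulas, one exercise arm versus usual care, n per arm**
- Design effect in the exercise arm: DE = 1 + (m − 1) × ICC.
- True variance of the difference: (σ²/n)(DE + 1). The unclustered analysis uses (σ²/n) × 2.
- Ratio of true to reported standard error: R = √((1 + DE)/2).
- True error: 2 × (1 − Φ(1.96/R)).

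Example, m = 3 and ICC 0.10: DE = 1.20, R = √1.10 = 1.049, error = 2 × (1 − Φ(1.869)) = 6.2%.

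| m | R at ICC 0.01 / 0.05 / 0.10 | True error |
|---|---|---|
| 1 | 1.000 / 1.000 / 1.000 | 5.0% / 5.0% / 5.0% |
| 2 | 1.002 / 1.012 / 1.025 | 5.1% / 5.3% / 5.6% |
| 3 | 1.005 / 1.025 / 1.049 | 5.1% / 5.6% / 6.2% |
| 5 | 1.010 / 1.049 / 1.095 | 5.2% / 6.2% / 7.4% |

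**Does the random centre factor repair this?** Simulation under no treatment effect (40,000 runs), with the extra variance in the exercise arm only, gave these error rates for a model with a random centre intercept:

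| Setting | ICC 0 | 0.01 | 0.05 | 0.10 |
|---|---|---|---|---|
| 3 hospitals as centres, m = 3 | 4.9% | 5.2% | 5.9% | 6.3% |
| 3 hospitals as centres, m = 5 | 5.0% | 5.3% | 6.2% | 7.4% |
| 8 exercise sites as centres, 9 per arm, effect common to the site | 5.0% | 5.3% | 7.9% | 10.2% |

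The t-test behaved similarly (5.1–9.7% over the non-zero ICCs). With no clustering both tests hold their level, so the excess comes from the clustering. The last row shows what happens if a site or therapist effect spans several blocks. Its 8 sites and 9 patients per arm are illustrative and are not in the documents.

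**Exercise + diet versus exercise.** Both arms sit in the same training groups, so a group effect largely cancels from their difference.

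**The case against.** The strongest reply is that the article condenses its analysis into one paragraph, and an unseen analysis plan may spell out the random effects. The text says only that centres are a random factor; it does not exclude an arm-specific or lower-level term. That much stands. But the article does name the clustering term, and read as it is written, the term does not fit the delivery.

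It can also be said that the effect is small: loads are set individually, all sites use one training protocol, interventionists are trained, and many physiotherapy groups are tiny. This stands too, and it limits the size of the point. The 10% centre correction is no answer, because it changes the number recruited and not the standard error.

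A reader might infer more than the documents support:
- *That the error rate certainly exceeds 5%.* No ICC is given, so the statement is conditional on a positive one.
- *That the variance ratio reaches 1.30 and the error 8.6%.* These arise for both exercise arms pooled against usual care, with groups of 10 and ICC 0.10: (1.90/2 + 1)/1.5 = 1.30. The plan specifies no pooled contrast; the stated aim sets each intervention against usual care. Figures for groups of 4–10 alone also leave out the physiotherapy groups of 1–6 and the block sizes.
- *That the centre variance rests on only three units.* This holds only if 'centers' means the three hospitals. The article mostly uses the word for exercise sites, so the meaning is ambiguous. The point here does not depend on it.

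**Conclusion.** The point holds as a modest, conditional one. The stated clustering term does not capture correlation confined to the exercise arms, on either reading of 'centers'. If that correlation is positive, intervals for each exercise arm against usual care are too narrow. With an assumed ICC of 0.01–0.10, the two-sided error is about 5.0–6.2% when a training group holds one to three members of the same arm, and 5.2–7.4% when it holds five. The lower range rests on training groups following the randomisation blocks, which the documents suggest but do not state. Site or therapist effects that span several blocks would push the error higher. This does not invalidate the trial, but it is worth correcting before analysis because the correction is cheap.

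**What to change.** For all comparisons with usual care, short-term as well as long-term, replace the t-test or centre-only model with a partially nested mixed model:
- a random training-group effect that applies only to patients in the two exercise arms, with each usual-care patient treated as a singleton;
- exercise site or therapist in place of training group if groups are rolling or very small, since a group variance would then be poorly defined or poorly estimated;
- small-sample degrees of freedom (Satterthwaite or Kenward-Roger).

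State whether 'centers' means hospitals or exercise sites. Fixed effects for hospital and training setting are optional. Record the training-group, site or therapist identifier for every exercise-arm patient; the documents do not say whether a group identifier is kept, so this should be confirmed with the sites.

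The cost is slightly wider intervals against usual care, one extra data field and a few lines in the analysis plan. Treatment delivery does not change.

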## Discussion

The aim of this RCT is to evaluate the effects and cost-effectiveness of an exercise only intervention and an exercise + diet intervention on physical functioning, quality of life and -as an important secondary aim- post-transplantation weight gain and cardiometabolic risk after renal transplantation. It will cover a large range of relevant patient-centered and clinical outcomes, as well as cost-effectiveness analyses, to provide guidance for evidence-based care.

The ACT trial is a pragmatic RCT. This means that already in the trial phase, the intervention is aimed at and implemented by regular staff members in daily care. This also implies that the control condition can be less controlled than it would have been in an explanatory trial [24, 25].

In the present study we strive for a set-up to maximize external validity within the context of renal transplant care in the Netherlands, by working with physiotherapists in existing rehabilitation centers and physiotherapy practices, and with dieticians in the field of renal care. Hereby generalizability to the clinical setting in RTR population is offered, providing widely applicable high-quality evidence for healthcare policy makers. Evidence-based behavioral components are included in the study to facilitate behavior change and long-term behavior maintenance.

Another strength is the application of focus groups with both the participants as well as the various healthcare professionals, as these qualitative data will provide a wealth of detailed information of patients’ and professionals’ attitudes toward and experiences with the intervention, supporting future implementation.

The present RCT includes a relatively high number of participants. The exercise training is delivered in larger groups at rehabilitation centers, and in smaller groups with physiotherapy practices. Sub-analyses may reveal differences in outcome between settings. The diet intervention is done by renal dieticians which are familiar with this patient population. Other strengths include gold standard measurement of aerobic capacity, objective measurement of physical activity using step counters, bio-impedance and BMI measured by dieticians, and the use of 24-h urine biomarkers.

A limitation of the present study is its complexity. The RCT involves skills and experience of multiple healthcare professionals working at different centers, making it difficult to standardize intervention delivery. Another limitation is that the exercise intervention and exercise with dietary counseling groups are combined. This may lead to contamination between groups, as participants of the exercise + diet group may share dietary advice with the exercise only group e.g. during the exercise training sessions. Furthermore, participants entering the ACT trial already have a certain degree of motivation to improve their health and fitness through lifestyle. Therefore, control participants may have worked on their health and fitness in alternative ways. Another limitation is that the study took place only in the Netherlands.

The present study aims to provide evidence needed to guide decision making by clinicians and policy-makers in post-transplantation care. Furthermore, it will help develop guidelines for post-transplantation care in the Netherlands to further improve long-term outcomes of renal transplantation.

## Abbreviations

1RM: One repetition maximum
ACT: Active care after transplantation
BIA: Bio-impedance analyzer
BMI: Body mass index
CIS-20: Checklist individual strength
CONSORT: Consolidated standards of reporting trials
EQ-5D: EuroQOL 5 dimensions
HbA1c: Glucose-bound haemoglobin
KDQOL: Kidney disease quality of life
KG: Kilograms
Pmax: Maximal muscle strength
QALY: Quality-adjusted life year
RCT: Randomized controlled trial
RTR: Renal transplant recipients
SF-36: Short Form 36
SGA: Subjective global assessment
SPPB: Short physical performance battery
VO_2_peak: Peak Oxygen uptake, a measure for aerobic capacity
Wpeak: Peak load (Watts), as assessed during the symptom-limited cycle ergometry
